## Discussion

### Significance and Impact

#### Aim 1: Assess the Effect of a Comfort Coach on Patient Experience

Nonpharmacological interventions administered by a comfort coach have the potential to decrease anxiety, self-reported pain, and stress while improving functional status and overall patient experience in the hospital for cardiac surgery patients, which would mirror findings in pediatric and nonsurgical adult populations [15,19]. These findings would have a significant impact on adult cardiac surgical care and establish a comfort coach role in a multidisciplinary perioperative care team. In addition, these findings justify the dissemination of these techniques and the role of the comfort coach in other types of surgery. Although cardiac surgery elicits significant preoperative anxiety and postoperative pain, other types of surgery such as oncologic, obstetrics, and orthopedic surgery are all associated with high amounts of anxiety, pain, and opioid use [9,40].

#### Aim 2: Measure Differences in Inpatient and Outpatient Opioid Use and Postsurgical Health Care Utilization

The role of surgery in the opioid epidemic has been well described [73] through widespread overprescribing [38,46], with the amount prescribed shown to be the most significant predictor of opioid consumption [47] and development of new persistent opioid use among previously opioid-naive surgical patients [74-81]. In cardiac surgery, persistent opioid use has been shown to confer higher rates of complications, length of stay, and health care costs [37]. Efforts have focused primarily on decreasing opioid prescription [72,82-85], whereas nonpharmacological interventions have not been well described in surgical patients. Comfort coaches may provide a nonpharmacological method for further decreasing opioid use, which would complement and enhance ongoing efforts to decrease prescribing. By addressing concurrent anxiety and decreasing perceived pain, nonpharmacological techniques may serve as valuable tools in addressing the opioid epidemic and improving surgical care.

The effect of the comfort coach’s interventions on anxiety, pain, stress, and opioid use can also be measured through overall health care utilization. As patient anxiety and pain decrease while satisfaction and comfort increase, we expect them to be better equipped and more prepared to leave the hospital. In addition, whereas individual nonpharmacological techniques such as preoperative educational prompts [48,49], massage therapy [50], and music [34] have been tested within hospital settings, no trial has measured the effect of an individualized comfort coach utilizing individualized nonpharmacological techniques throughout the entire perioperative course, from preoperative clinic visit through 90-days of postoperative follow-up. An innovative aspect of this trial is sending different nonpharmacological tools home with patients based on their individualized preferences and continuing self-administered nonpharmacological techniques for 30 days postoperatively. We expect these sustained efforts to reflect decreased health care utilization through hospital length of stay, minimized or eliminated days spent in an extended care facility, prevented emergency room, urgent care, and unplanned doctor office visits, telephone calls, and readmissions, all of which may decrease health care costs.

#### Aim 3: Qualitatively Evaluate the Effectiveness of the Comfort Coach Intervention

We expect the comfort coach intervention to be extremely impactful. In contrast to testing 1 individual technique [50,86-88], the comfort coach intervention is a series of individualized nonpharmacological interventions administered by a trained coach incorporating patient preference and choice from a comfort menu. Qualitative analysis is essential to identify specific aspects of the comfort coach intervention, which were effective or ineffective, and answer *How?* and *Why?* to inform broader implementation. The findings from our qualitative study will prescribe how hospitals can expect to implement our findings efficiently. If the most impactful aspect of the intervention is the individual person, hospitals can focus on providing a companion for patients at critical moments in the perioperative process. If being coached were most impactful for patients, this would justify a certified comfort coach’s role with training in administering these specific nonpharmacological techniques. If patients find specific techniques most effective, these can be packaged into a scalable paper or electronic tool, which can be broadly implemented for surgical patients. Insight into why different aspects of the intervention were effective will guide further implementation.

#### Economic Implications on the Cost of Health Care

Previous evaluations within pediatric [52,53] and adult nonsurgical populations [17,18] have established decreased health care utilization and, consequently, health care costs associated with nonpharmacological interventions. Much of the effect of coaching by certified child life specialists on reducing health care costs has been attributed to the reduced need for anesthesia in imaging procedures [52,53]. Furthermore, coaching interventions have been associated with decreased opioid use duration and length of hospital stay [15-18,51].

We anticipate that our coaching intervention may have more profound impact when evaluated within an adult inpatient surgical population. Relative to nonsurgical and many other types of surgical populations, our cardiac surgical population has greater anxiety, more pain and opioid use, and longer average lengths of stay. Even with our conservative effect sizes estimating a 10% reduction in the published mean episode payments for CABG and valve surgery [30,31], we anticipate savings within Michigan to be approximately US $54 to 80.4 million annually if our comfort coach intervention were disseminated across all 33 nonfederal cardiac surgical hospitals.

By decreasing health care utilization, the comfort coach intervention may have profound economic implications, particularly in decreasing the amount of time patients spend in the hospital. For payers, less health care utilization will decrease episode payments, which reach up to US $15 billion annually in the cardiac surgery population [29-32]. For hospitals, decreasing individual patient health care utilization could mean an increase in new patient admissions and increased efficiency of patient throughput, which carries increased importance in the current era of value-based reimbursement.

### Barriers to the Project

#### Healthy Volunteer and Placebo Effect

Whereas patients receiving the control treatment may report improvement because of the healthy volunteer effect [89], patients receiving intervention may report improvement in anxiety, pain, and satisfaction by virtue of the placebo effect of having a comfort coach. However, we feel that this *placebo effect* is a real effect that we hope to measure through this intervention. Our project’s qualitative component aims to assess what works, what does not work, and even furthermore, how the intervention does or does not work. Accordingly, we feel the potential effect of having a designated coach to be an important measure.

#### Spillover Effects

Our trial may be susceptible to spillover effects, both internally in our intervention and from external forces such as competing institutional interventions. Specifically, opioid reduction efforts for specific general surgery procedures at our institution have demonstrated spillover effects into additional general surgery procedures, with corresponding reductions in opioid use found [83]. Similar efforts around perioperative education and opioid prescribing have taken place in cardiac surgery and may affect the opioid use secondary outcome if current prescribing and use are too low to observe significant changes. Internal spillover effects may also occur, such as nursing and other care team members observing comfort coach interventions and incorporating these nonpharmacological techniques into their usual care. We attempted to mitigate this effect by conducting in-service educational sessions with physicians, advanced practice team members, and nurses to make each stakeholder aware of the trial and the intervention being tested. In addition, if a trend of improvement in the control arm of this trial over time is observed, this difference over time will be treated as the effect size of spillover, and we will report it as such in the trial analysis.

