#### COVID-19 Effect

Approximately 20% of patients during the trial will have received inpatient care either during or after the peak of the COVID-19 pandemic. The usual amount of fear and anxiety elicited by cardiac surgery and the associated recovery period enhance patients’ typical need for close physical, emotional, and psychological support from their loved ones. The hospital-wide policy prohibiting all visits during COVID-19 may cause an increase in the levels of fear and anxiety caused by surgery and recovery owing to enhanced feelings of isolation, separation, and possibly even abandonment—at such a crucial time of need—by the most important loved ones in their lives. These policy changes may enhance the impact of a comfort coach on the intervention arm, simply by adding more human contact through a caring and empathetic individual at these critical touchpoints of care, irrespective of the nonpharmacologic therapy the coach provided.

In contrast, the control patient group during the COVID-19 pandemic may be at a potential disadvantage compared with the control patient group before COVID-19 because the pre-COVID control group had the usual level of support from family, friends, and significant others. These 2 opposing effects, namely, a potential enhancement for the intervention group and additional tension and anxiety from isolation and separation among the control group, may have affected the study results. However, it is also possible that patients in the intervention group during COVID-19 remained anxious and fearful despite having a comfort coach because of separation from loved ones, fear of infection in the hospital, or other factors. Although we cannot mitigate the impact of COVID-19, we will perform a subset analysis of patients who received care during COVID-19 to evaluate for any significant differences in our data.

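### An improvement over time in the control arm is to be reported as the size of spillover, but a one-arm time trend cannot identify spillover

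*Protocol article*

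**What the plan says.** The rule stands in the Discussion of the protocol article, under Barriers to the Project, Spillover Effects. Its trigger is: "if a trend of improvement in the control arm of this trial over time is observed". Its consequence is: "this difference over time will be treated as the effect size of spillover, and we will report it as such in the trial analysis".

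The same section defines spillover broadly, as "spillover effects, both internally in our intervention and from external forces such as competing institutional interventions". The internal route is "nursing and other care team members observing comfort coach interventions and incorporating these nonpharmacological techniques into their usual care". For the external route it reports: "Similar efforts around perioperative education and opioid prescribing have taken place in cardiac surgery and may affect the opioid use secondary outcome".

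Two neighbouring sections bear on the control arm. Healthy Volunteer and Placebo Effect gives the healthy volunteer effect as a reason why controls may report improvement, without saying that it changes over calendar time. COVID-19 Effect says that "the control patient group during the COVID-19 pandemic may be at a potential disadvantage compared with the control patient group before COVID-19", puts about 20% of patients in that period, and plans: "we will perform a subset analysis of patients who received care during COVID-19 to evaluate for any significant differences in our data".

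**The concern.** The rule turns an observed trend directly into a named causal quantity. A control-arm trend has at least four components:

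- internal contamination;
- external programs;
- other secular or case-mix drift;
- sampling error.

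They have different consequences. Contamination makes controls resemble treated patients and shrinks the contrast between arms. A program that reaches both arms equally moves both means and leaves the contrast alone. One number under the heading of spillover merges the two, and the article gives no way to split them.

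What is at stake is interpretation. A figure published as the measured size of spillover invites the reader to add it back to the treatment effect, or to excuse a null result with it. If the trend were secular or noise, that reading would be wrong.

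**Working it through.** **Inputs.** From Power Analysis: 3-day difference in days at home, SD 6 days, 80% power, two-sided alpha 0.05, planned total 154. From Patient Enrollment and Randomization: 144 enrolled at the pause. From COVID-19 Effect: about 20% treated during or after the peak. Assumed here: 1:1 allocation (77 controls of 154, or 72 of 144), even accrual, an early/late split at the midpoint, and SD 6 within the control arm.

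**Step 1. The protocol's own figure.** A two-sided two-sample t test with d = 3/6 = 0.5 needs 63.8, so 64, per arm: 128 in total, as stated. The SD and design effect are therefore a fair scale for what follows.

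**Step 2. Chance variation in a control-arm change.** With h controls in each half, SE = 6 × √(2/h).

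| Controls | h | SE (days) | 95% limits, 1.96 × SE |
|---|---|---|---|
| 72 | 36 | 1.41 | ±2.8 |
| 77 | 38.5 | 1.37 | ±2.7 |

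With 77 controls, 80% power is reached only for a true change of about (1.96 + 0.84) × 1.37 = 3.8 days, more than the 3-day design effect.

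**Step 3. What would be reported if nothing changed.** With no true change the estimate points to improvement about half the time. When it does, its average is SE × √(2/π) = 1.37 × 0.80 = 1.1 days. For a fitted straight line from start to end of accrual, SE = 6 × √(12/77) = 2.37, and the corresponding average is 1.9 days. These are 36% and 63% of the design effect.

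**Step 4. Identification.** Take a true treatment effect of 3 days and a control-arm trend that rises linearly by 2 days from start to end. Suppose secular change reaches both arms equally and contamination reaches controls only. Averaged over accrual, a linear 2-day contamination costs the contrast 1 day.

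| Source of the 2-day trend | Control-arm trend | Expected difference between arms |
|---|---|---|
| All secular | 2 | 3.0 |
| Half and half | 2 | 3 − 0.5 = 2.5 |
| All contamination | 2 | 3 − 1 = 2.0 |

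A simulation with 77 per arm gave the same picture: mean control trends of 2.02, 2.00 and 2.00, and mean arm differences of 2.98, 2.50 and 2.00. The control arm shows the same trend in all three cases, so it cannot say which one holds.

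**Step 5. The COVID-19 subset.** 0.2 × 154 = 30.8, so about 31 patients against 123. An arm-by-period estimate has SE = 6 × √(2/15.5 + 2/61.5) = 2.41 days (0.40 SD), so 95% limits of about ±4.7 days.

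**The case against.** Several points on the other side are sound.

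- A reader might infer that the plan contradicts itself by naming opioid and education programs as causes other than spillover. It does not: its definition counts competing institutional programs as external spillover. What stands is that internal and external routes are pooled under one figure although they act differently on the contrast.
- A reader might infer that COVID-19 is named as a cause of control-arm improvement. The text says the opposite. Visiting restrictions may disadvantage controls, so on the protocol's own account they would hide an improvement and the rule would not fire. COVID-19 confounds the trend but is not offered as a source of improvement.
- Triggering the rule only on improvement is understandable, because the mechanisms described predict improvement. The test, threshold and time scale may be in a fuller document, and their absence is not counted here. The defect is the causal label, which the article does state.
- The statement sits in the Discussion, and nothing says that the figure will adjust the treatment effect. That limits the consequence, but the text does promise to report it in the trial analysis.
- The COVID-19 wording leaves the comparison open, so it cannot be said to look only inside the subset. An interaction has only about 24% power for 0.5 SD, so it is no remedy for imprecision.
- The early/late split and the use of days at home are illustrative. The article links the named programs to opioid use, not to days at home.

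**Conclusion.** The point holds for the spillover rule. Followed as written, the protocol would report a mixture of contamination, shared secular change, case-mix drift and chance as the effect size of spillover. With SD 6 days and 72 to 77 controls split evenly, chance alone spans about ±2.7 to 2.8 days against a design effect of 3 days. These figures rest on 1:1 allocation, even accrual and a midpoint split; the identification problem does not depend on them.

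The stronger reading, that the trial's main result is compromised, is not supported. The primary endpoint is compared between arms with a t test that does not use this quantity, and change shared equally by both arms does not bias that comparison. The harm is a mislabelled supplementary result that could be used to explain the main one. It should be corrected, but it does not threaten the trial's validity.

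On COVID-19 the conclusion is conditional: only if the subset analysis is meant to show whether the treatment effect changed is a subset result alone the wrong quantity.

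**What to change.** Replace the rule under Spillover Effects. Report the control-arm trend by calendar time with its 95% CI, show the intervention-arm trend beside it, and name spillover only as one possible explanation. The second trend helps to show whether a change was shared, but it does not by itself prove contamination.

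Under COVID-19 Effect, state which comparison is meant. If the question is whether the treatment effect changed, fit arm, period and arm-by-period in the full sample, report the interaction with its CI, and label it exploratory. Define period by date of inpatient care. Enrollment date would not serve: 144 of 154 patients were enrolled before the pause, which leaves 10 for the later period instead of about 31.

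The cost is a change of wording and one extra model, with no new data. The downside is imprecision, about ±4.7 days for the interaction with 31 against 123 patients; the interval would show this openly.

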#### Generalizability

If the intervention tested is beneficial, a generalizable implementation of trained comfort coaches for surgical patients may be questioned. To overcome this generalizability barrier, we will first consider our qualitative third aim to describe how these techniques were effective or ineffective. If specific techniques are effective, they can be translated into a scalable paper or electronic tool that can be broadly implemented. Second, the health care utilization is found to be lower among those who receive a comfort coach, we plan to financially quantify this difference with 90-day episode payments between arms and perform a cost-effectiveness analysis incorporating the cost of comfort coaching to demonstrate cost savings that can be used by other health systems to assess whether to implement these methods.

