###### Postsurgical Health Care Utilization

The primary endpoint of this trial is a composite outcome defined as the total number of days spent at home within the first 30 days after surgery. Each partial or full day spent in the hospital (during index or readmission hospitalization), at any extended care facility, emergency room, urgent care center, or doctor’s office for an unplanned visit will be subtracted from 30 to generate the total number of full days spent at home. This number will reflect total health care utilization within the immediate postoperative period, with lower values indicating more utilization. The number of days in an extended care facility, outside hospital emergency room or urgent care visits, and readmissions are routinely discussed at the 30-day postoperative clinic appointment and will be captured through a combination of chart review by 2 study team members and conversations with patients. In addition, the number of telephone calls made by each patient or patient’s family member to the University of Michigan hospital system regarding the clinical concerns of the patient within the first 30 postoperative days will be captured through chart review and independently verified by 2 study team members. If necessary, we will then use Michigan Value Collaborative data to quantify differences in health care utilization by comparing total and component 90-day episode payments among Medicare, Blue Cross Blue Shield of Michigan, and Medicaid beneficiaries, as our team has previously done in both coronary artery bypass (CABG) [31] and aortic valve replacement [30] studies in Michigan.

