##### Power Analysis

Our primary endpoint is composite of health care utilization, defined as the total number of days spent at home within the first 30 days after surgery. Secondary endpoints include mean GAD-7 and PHQ-9, KCCQ-12, Picker Patient Experience Questionnaire, IES-R, and Brief Pain Inventory Scores and mean inpatient and outpatient opioid use.

We will compare mean days with a two-tailed *t* test and set the power of this study at 80% with alpha (Type I error) of .05 and the Cohen *d* effect size (defined as the difference in means divided by standard deviation) between medium (0.5) and large (0.8) [69,70], which yields a minimum sample size of 52 patients to detect a large effect size and 128 to detect a medium effect size [71]. Incorporating 20% missingness, a sample size of 154 patients will adequately detect a medium effect size. We next verified this statistically derived sample size with clinically relevant examples. Although most large series reporting opioid use report the median and interquartile range of OME [47,72], our sample size should be sufficient to satisfy the central limit theorem and use mean values. At our institution, the mean opioid use after sternotomy in 2017 was 200 OMEs. We estimated that to detect a 30% reduction in opioid use (mean 140 OMEs) with a standard deviation of 125 OME in the control and 100 OME in the intervention arms, a sample size of 114 would be required. For composite health care utilization, demonstrating a 3-day difference between the arms with a 6-day standard deviation would detect by a total sample size of 128 patients. With 154 patients, we should have adequate power to detect a difference in our primary outcomes for aims 1 and 2.

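### The 90-day payment and cost-effectiveness analysis is planned only if utilization is found lower with the coach, so estimated savings are selected upward and no net cost is planned otherwise

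*Protocol article*

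**What the plan says.** Two sections of the protocol article describe the payment analysis.

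- **Barriers to the Project, Generalizability.** The trigger is that "the health care utilization is found to be lower among those who receive a comfort coach". The word *if* has dropped out of the sentence, but it can only be read as a conditional. The consequence is "we plan to financially quantify this difference with 90-day episode payments between arms", and the authors will then "perform a cost-effectiveness analysis incorporating the cost of comfort coaching to demonstrate cost savings". The results are meant to help other health systems decide whether to adopt coaching.
- **Methods, Postsurgical Health Care Utilization.** "If necessary, we will then use Michigan Value Collaborative data to quantify differences in health care utilization". No criterion is given for when this becomes necessary, and no direction is stated. The method is given as "comparing total and component 90-day episode payments among Medicare, Blue Cross Blue Shield of Michigan, and Medicaid beneficiaries".

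The utilization measure is the primary endpoint, counted from surgery: "The primary endpoint of this trial is a composite outcome defined as the total number of days spent at home within the first 30 days". The Power Analysis section, which sets alpha at .05, states: "We will compare mean days with a two-tailed *t* test and set the power of this study at 80% with alpha (Type I error) of" that size. That comparison does not depend on any earlier result.

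No section commits to the payment or cost-effectiveness analysis regardless of the utilization result. The article also does not say whether *lower* means a lower point estimate or a statistically significant reduction.

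**The concern.** The Generalizability text makes the existence of an economic estimate depend on the observed direction of the main result. This has two consequences.

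1. **A gap.** If utilization is equal or higher in the coach arm, no net cost is planned. That is the case in which the coach is most likely to be a pure added cost. The Preliminary Data section says that the full trial calls for a full-time dedicated coach, so this cost is real.
2. **A selection effect.** Payments and utilization come from the same patients. A trial that shows lower utilization partly by chance will, if the two are positively correlated, also show lower payments partly by chance. Estimating payments only in such trials overstates savings on average.

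The figures are intended for hiring decisions elsewhere. The section on economic implications already projects savings of US $54 to 80.4 million a year within Michigan, so readers will look to this analysis to confirm or correct that expectation.

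**Working it through.** **Inputs.** From Power Analysis: a 3-day difference, SD 6 days, two-sided alpha .05, 80% power, total 128, 20% missingness, 154 enrolled. Assumed: 1:1 allocation (the ratio is not stated), and that utilization in the trigger is the days-at-home composite.

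**The plan's own figure.** n per arm = 2 × (1.96 + 0.842)² × 6² / 3² = 62.8, so 63 per arm (126 in total) by the normal approximation. The t-test version gives 63.77, so 64 per arm and 128 in total. The stated 128 is reproduced.

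**Standard error of the difference.** SE = 6 × √(2/n).
- n = 64 per arm (the 128 in the plan): SE = 1.06 days.
- n = 61 per arm (154 × 0.8 = 123.2 evaluable, halved and rounded down): SE = 1.09 days.

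**Selection effect.** Let δ be the true reduction in utilization days and c the threshold that triggers the analysis. Then

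E[estimate | analysis run] = δ + SE × φ(a) / (1 − Φ(a)), with a = (c − δ)/SE.

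For *any lower*, c = 0. For *significantly lower*, c = 1.96 × SE. Example at δ = 0, any lower: a = 0 and φ(0)/0.5 = 0.798, so the overstatement is 0.798 × 1.06 = 0.85 days (0.87 at 61 per arm).

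Overstatement in days, with the share of trials in which the analysis is run in brackets. Each pair is 64 / 61 per arm.

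| True reduction | Any lower | Significantly lower |
|---|---|---|
| 0 days | 0.85 / 0.87 (50%) | 2.48 / 2.54 (2.5%) |
| 1 day | 0.33 / 0.35 (83% / 82%) | 1.63 / 1.69 (16% / 15%) |
| 2 days | 0.07 / 0.08 (97%) | 0.90 / 0.95 (47% / 45%) |
| 3 days (design) | 0.01 / 0.01 (99.8% / 99.7%) | 0.36 / 0.40 (81% / 79%) |

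With 77 per arm (no missing data) the pattern is the same and the values are slightly smaller.

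**Carrying this to payments.** Under joint normality the payment difference takes ρ times the same bias, in units of its own SE, where ρ is the correlation between the two estimated differences. The article gives no ρ, so 0.3, 0.5 and 0.8 are assumed as a range (64 per arm):

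- No true effect, any lower: 0.24, 0.40, 0.64 SE of the payment difference.
- No true effect, significantly lower: 0.70, 1.17, 1.87 SE.
- 3-day effect, any lower: 0.00, 0.00, 0.01 SE.
- 3-day effect, significantly lower: 0.10, 0.17, 0.27 SE.

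The payment data cover only beneficiaries of three payers. If some patients fall outside these, the two estimates share fewer patients and ρ is smaller. The article gives no SD for payments, so none of this can be put in dollars.

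If the analysis is run whatever the utilization result, this bias is zero at every true effect.

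**The case against.** Five points can be made in the plan's defence.

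1. **The economic result need not be favourable.** A reader might infer that the rule can never produce an added cost. The text does not support that. The trigger is utilization over 30 days, while the analysis covers 90-day payments and includes the cost of the coach. A small gain in utilization may cost less than the coach, and payments after day 30 may run the other way. This stands: selection is on utilization, not on savings.
2. **The Methods wording has no direction.** The Postsurgical Health Care Utilization section speaks of differences, not reductions. This stands too: the directional rule rests on the Generalizability sentence alone. But the Methods wording sets no criterion, so it does not commit the authors to the analysis either.
3. **The bias is small if the design assumption is right.** At a true 3-day effect it is negligible under one reading and about 12% (0.36/3) under the other. This is correct. The true effect is unknown, however, and the bias grows as the effect shrinks.
4. **The figures in days do not describe a biased result.** The days-at-home comparison is done unconditionally and is unaffected. This is correct: the days only illustrate the selection, and the affected quantity is the payment estimate.
5. **The stakes are limited.** Payments and cost-effectiveness are neither primary nor secondary endpoints, and a null primary result would already show no 30-day offset to the coach's cost. This supports a low severity. It does not supply the missing 90-day net cost.

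A condensed article may leave the definition of *lower* and the costing details to a fuller document. The conditional rule itself is stated here and is fair to question.

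**Conclusion.** The point holds as a low-severity one about a supplementary analysis. The Generalizability section plans the payment and cost-effectiveness work only after a favourable utilization finding and frames it as showing savings. The Methods make the same comparison depend on an undefined necessity. As written, no net cost is planned for equal or higher utilization, and savings estimated under the rule are biased upward for any positive correlation between payments and utilization.

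The size of the bias depends on the true effect and on what *lower* means. On the utilization scale it runs from about 0.01 days (3-day effect, any lower) to about 2.5 days (no effect, significance required, which happens in only 2.5% of trials). These figures assume SD 6, 61 to 64 per arm, 1:1 allocation and normality. The bias in dollars cannot be derived from the document.

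Two stronger readings should be avoided: that every economic result would be favourable, and that the primary result is biased or a null hidden. The text supports neither.

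**What to change.** Reconcile the two sections with one commitment: total and component 90-day payments, and net cost including the cost of the coach, will be compared by randomized arm among beneficiaries of the named payers, with 95% CIs, whatever the direction or significance of the utilization result. In the Methods, delete the opening *If necessary*. In Generalizability, remove the condition and change the purpose from demonstrating savings to estimating net cost.

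The cost is a wording change plus an analysis already contemplated, from a data source the team has used before. Enrolment, treatment and trial data collection do not change. The downside is some analyst time if the primary result is null, and possibly an unfavourable cost figure to report.
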